## Abstract

Background: Community-dwelling older clients are becoming increasingly complex. Detecting this complexity in clinical practice is limited, with greater reliance on community nurses’ clinical judgment and skills. The lack of a consistent approach to complexity impacts the level of care and support for older clients to remain in their homes for longer. Objective: To examine the effectiveness of the Patient Complexity Instrument (PCI) in addition to nurses’ clinical judgment to enhance detection of complexity, and subsequent older clients’ resource allocation compared to usual nursing assessment. Design: A pragmatic randomized controlled trial will be conducted within a community nursing service in regional Victoria, Australia. Clients 65 years and over referred to the service who are eligible for Commonwealth Home Support Programme (CHSP) funding will be randomized into Control group: usual nursing assessment or Intervention group: usual nursing assessment plus the PCI. Nurse participants are Registered Nurses currently employed in the community nursing service. Results: This study will explore whether introducing the PCI in a community nursing service enhances detection of complexity and client care resource allocation compared to nurses’ clinical judgment based on usual nursing assessment. Conclusion: This protocol outlines the study to enhance the detection of complexity by nurses delivering care for community-dwelling older people in the regional Australian context. The findings will inform the use of a standardized tool to detect complexity among community-dwelling older Australians.

## 1. Introduction

### 1.1. Global Ageing Population and the Implications

Countries around the world, including Australia, are faced with an increasing ageing population. Trending indicates that by 2050, “one person in every five will be over 60 years of age or older” [1]. This demographic shift impacts on the number of people needing support to remain at home. As people age, if their choice is to stay at home, many will require more support. Their needs may increase with varying degrees of complexity depending on their ailments, social situation, access to resources and safety of their environment [2]. Therefore, along with the increasing number of people needing support, their care needs are more complex. 

As new models for chronic conditions and post-discharge care options increase, people are not staying in hospital for as long [3,4,5,6]. People are being discharged with a higher level of care required, with a consequence of increasing complexity of the community-dwelling older people [7,8,9,10] and increased reliance on caregivers for support [11]. Huber et al. recognized that the increasing prevalence of multimorbidity is also impacting care in the community [10]. The flow-on effect is increasing workload pressure on the community nursing services to deliver the complex care to maintain the independence of older people in the community and safety at home.

Internationally, strategies are being developed to support growing ageing populations and improve their health care. Australia, United Kingdom and Canada employ similar strategies including improving access to home and community aged care, support for carers, and reducing the need for residential aged care [12,13,14]. These governments recognize the impact of an ageing population, increase in chronic disease prevalence and the need to think differently about how and where healthcare is delivered. The Royal Commission into Aged Care Quality and Safety in Australia reported that caring for older people in acute hospitals and residential aged care is costly on the healthcare system and there is a need to better develop community programs to support people who wish to remain independent at home [15,16].

### 1.2. Ageing Population in Australia and the Implications

In Australia in 2015, the number of people aged 65 years and over accounted for 15% of the population [17]. Around six out of ten people aged 65 years and over experience 33% of the burden of ill health and say they are in less than very good health [17].). This data has contributed to changes implemented in the health care sector in general. One area of change has been the care of older people in the community. The Australian Government recognized the challenges of an ageing population that is rapidly changing and established the CHSP in 2011 [18]. With less affordable residential care places available in regional and rural areas, there is an 84% increase of people requiring home care over the past 10 years [19]. In 2018 the Australian Government launched additional initiatives aimed at keeping older people well at home and engaged in the community, whilst reducing the need for hospital admission and delaying admission to residential aged care [18,19,20,21]. These initiatives built on strategies implemented since 2011 and have been reviewed again in the national health care reform agreement and 2020–2025 addendum [14,22]. In order to support the CHSP and subsequent initiatives, The National Screening and Assessment (NSAF) was implemented in Australia in 2018 and consisted of two types of home-based assessments [23]. The first is a home support assessment and second is an aged care comprehensive assessment. The home support assessment is required for a client to be eligible for CHSP services and the comprehensive assessment is required for home care package eligibility. The NSAF is a useful starting point for client assessment however, it is difficult to develop rapport in one visit and determine all care required. The nursing assessment using the NSAF may need to be conducted over 2–3 visits to develop a more comprehensive picture of how the client is managing.

### 1.3. Factors Contributing to Complexity

The World Health Organization (WHO) identified that “by the age of 60 years, the major burden of disability and death arises from age-related losses in hearing, seeing and moving, and conditions such as dementia, heart disease, stroke, chronic respiratory disorder, diabetes and musculoskeletal conditions such as osteoarthritis and back pain” [24]. The prevalence of multimorbidity (two or more diseases) is high among older people with 74.6% have multiple chronic conditions [25]. Multimorbidity adds another layer to complexity because of the need for various treatments and coordination of multiple care services. As well as multimorbidity, socioeconomic position, social support options, psychological stress, inadequate nutritional intake, reduce physical activity all have an impact on the family’s ability to assist and the variety of services needed to support the older person [26,27]. These factors influence health outcomes and require comprehensive assessment and monitoring [28].

Ageing is an accumulation of molecular and cellular damage over time which leads to gradually decreasing physical and mental capacity, while increasing risk of diseases and eventually, death [29]. WHO reported that “the loss of ability typically associated with ageing is only loosely related to a person’s chronological age” [29]. Yet, some older people continue to enjoy very good health and function independently while others are frail and require significant supports. The presence of one or more of mobility loss, malnutrition, visual impairment and hearing loss, cognitive impairment or depressive symptoms can be identified as contributing to a declining physical and/or mental capacity [24]. These factors contribute to client complexity and the ability to continue to do what they value most.

Before complexity is measured, it needs to be defined. An overview of the literature indicates that complexity is sometimes used interchangeably with frailty, yet they are different [30]. Frailty is described as a physical wellbeing state, linked to fatigue, resistance and aerobic capability, other illnesses, loss of weight and the client’s awareness of their health [31]. However, this description does not take into consideration personal and environmental factors. Gobbens et al. suggest that frailty could also be considered dynamic when these additional factors are considered [32]. Encompassing the physical as well as psychosocial and environmental aspects of a person is what makes complexity dynamic, meaning that the complex client can shift between recovery and relapse into a complex state [30]. Some definitions of frailty are outdated and place greater emphasis on the medical model view of frailty. More recent definitions consider the multidimensional nature of frailty [33]. In contrast, definitions of complexity are fewer, and there is an increasing reference to the need to determine a client’s complexity. Determining the level of complexity involves conducting a comprehensive assessment that also considers the clients’ level of engagement, clinical need, social contact, family/carers, resources, and safety [2].

Nurses working in the community report that clients are becoming more complex; hence more resources and time are required for nurses to deliver the appropriate care. Contributing to this complexity are factors affecting family structures and supports. For instance, children or family members are no longer live within proximity to their parents or older family members to render assistance or they work full-time to support their own immediate families. Older people wish to continue to live in and actively contribute to their community, and families support the idea of their older parents remaining at home for as long as possible. Current practice and systems in the care of older people need to change from the traditional provider-centered model to a value-based model the enables the older person and their family to be more involved and share their needs and priorities [34,35]. All these factors combined impact a client’s ability to manage independently. A change in one or more of these factors, e.g., the loss of a partner or a new diagnosis, can have an impact on the level of care required, hence the dynamism of client complexity.

### 1.4. Assessment of Older People by Nurses

Nurse-led assessments in the community result in decisions made and actions planned with the older client, regarding referrals and additional resources. The client’s General Practitioner (GP) is informed of community nurse-led assessment but is not the decision maker of care coordination. This contrasts with the bulk of assessments for older people where nurses either independently or as part of a multidisciplinary team collect data but are involved in the care decision making. This is an important difference to other geriatric assessments conducted by nurses such as the primary care assessment for people 75 years and older [36] where the GP makes decisions with the client. InterRAI is a subscription based comprehensive suite of assessments that can be completed by any trained health professional [37], this tool has been adapted for use in home care settings in recent years. There are also recent studies with nurses completing the geriatric assessment data, however the geriatrician will make decisions regarding actions [38,39,40]. In Australian community-based programs, multidisciplinary teams are growing but there is limited access to geriatricians. The assessment tool, clinical judgment clinical experience is important in the decision-making process for complex clients.

Given the range of factors that need to be considered when determining the care needs of an older person, different approaches to assessment have evolved [41]. Comprehensive assessment and monitoring require standardized, robust, and multidimensional tools to assist community nurses to detect client complexity. Such tools need to also consider psychosocial factors and biomedical factors to enable streamlining of clinical care and supportive resources required for the complex client. Clinical judgment is also recognized as an important factor in determining the care needs of an older person [41]. Structured assessment tools alone do not encourage a person-centered model, as clinical judgment is required to link all the aspects of a structure assessment together. 

A scoping literature review was conducted to identify a potential standardized tool to trial. The review methodology and results will be published elsewhere. In summary, a search was performed in Medline and CINAHL. Five tools were identified but only one, the Patient Complexity Instrument (PCI) [2], met the criteria. 

### 1.5. Aim and Objectives

The Improving Detection of Patient Complexity in the Community (ImPaCt) is a trial of the PCI within the community nursing service to improve detection of client complexity in regional Victoria. The primary objective is to explore whether adding the PCI to the usual assessment process could enhance the detection of the complexity of clients and support the clinical judgment. The secondary objective is to explore whether using the PCI derived client complexity could facilitate appropriate resource allocation; these resources being the time allocated to providing clinical care to the complex client or referrals completed to support the client. The study will also explore issues around the feasibility and acceptability of the PCI in community nursing.

This study aims to answer the question “Does the PCI in addition to usual assessment, enhance nurses’ detection of complexity and delivery of appropriate allocation of care for community dwelling patients aged 65 and over?”.

The primary null hypothesis is the addition of the PCI has no effect on nurses’ detection of patient complexity compared to usual assessment alone. The secondary null hypothesis is the addition of the PCI does not enhance the allocation of appropriate resources according to the client’s complexity. 

Ethical approval has been provided by the researchers’ employer and the supporting University reference number (blinded). The trial has been registered with the Australian and New Zealand Clinical Trials Registry (blinded).

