### 2.6. Sample Size

Initial data will be used to conduct a post hoc sample size calculation. Up to *n* = 34 (all) nurses in the community nursing service will make up the nurse participant sample. These are nurses making up the team who would normally be available to conduct assessments on referred clients. Based on the number of new referrals expected over three-month period, a convenience sample of up to *n* = 180 patient assessments (90 per group) will be targeted and up to *n* = 27 (all) nurses in the service will make up the nurse participant sample. Due to the pilot nature of the study, formal sample size calculation is not critical. Pilot studies by their nature are not aimed at establishing a definitive effect, however a rationale for sample size basis such as described above is deemed sufficient [44,45].

Using our early pilot data, post hoc sample size calculation was performed based on the proportions of the level of complexity rating in the ImPaCt study. A minimum total sample *n* = 138 patient assessments, i.e., 69 per group (Figure 1) will be required in definitive trial to detect a significant difference in proportions relating to a high level of complexity rating between the control (23.1%) vs. intervention (5.7%), odds ratio = 4.97, power = 0.8 and *p* < 0.05.

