### 2.9. Outcomes

The primary outcome of the RCT component is client complexity rating (low, moderate, or high) as measured using the PCI (intervention) or usual assessment nurse judgment alone (control).

The first secondary outcome is the addition of nursing care interventions after initial assessment. These are the required interventions for the client based on the assessment outcome and the detected level of client complexity. The nursing care interventions will be categorized as medication support, wound care, referrals and liaison and others. The second secondary outcome is the nursing care time added in minutes. This is the additional time that may be allocated to the delivery of the nursing care interventions for the clients following assessment and detected level of client complexity. 

Data will be collected using baseline and follow up surveys (File S1 and S2 in Supplementary) completed by participating nurses allocated to the intervention group pre- and post-PCI use. The survey will be administered electronically or via paper form. It will be supplemented with field notes and observations recorded by the researcher throughout the study. Any focus groups or interviews conducted will be recorded for transcription.

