### 2.10. Data Analysis

Statistical analysis will be carried out in IBM SPSS Statistics Version 24 (IBM Corp, New York, NY, USA). For quantitative data analysis, statistical significance will be indicated by *p* < 0.05.

Participant characteristics and survey data will be analyzed and presented using summary descriptive statistics. Statistics will include mean and standard deviation for continuous data, median and interquartile range for ordinal data and percentage and 95% confidence interval for nominal data. Comparative univariate statistics will be conducted to test for differences between control and intervention characteristics. Parametric and or non-parametric statistical tests will be used to compare the groups.

Currently the PCI has no cut-offs for the level of complexity ratings. Preliminary data will be used in a receiver operating characteristics (ROC) analysis to determine complexity rating cut-offs (categorized as low, moderate, or high) with usual care complexity rating as the criterion. Categorial level of complexity rating as a primary outcome will be compared between control and intervention groups using the Chi-square independence test.

For the first secondary outcome, modification of nursing interventions (addition or subtraction of nursing interventions), between group comparisons will be performed on distribution of intervention categories. The second secondary outcome, clinical time will be compared between the study groups using ordinal regression. Clinical time as the dependent three level categorical variable. Age and nurse’ years of community experience will be covariates, while gender, reason for referral, group allocation (intervention or control) and level of complexity rating will be factors in the regression analysis.

Qualitative data collection will be from surveys, additional information regarding nursing interventions, nurse’s feedback, field notes and observations recorded by the researcher. Audio-recorded information from focus groups will be transcribed verbatim. Inductive thematic analysis has been chosen because this will ensure that themes emerge from the data (bottom-up approach). Analysis will be conducted using Braun and Clarke’s phases which include (1) data familiarization, (2) initial code generation, (3) theme search, (4) review of themes, (5) define and name themes [46].

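### The secondary hypothesis is about care matched to complexity, but the stated outcomes and tests address only the amount and type of care in each arm

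*Protocol article*

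**What the plan says.** All references are to the protocol article.

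- **Hypothesis (section 1.5).** The secondary null is that "the addition of the PCI does not enhance the allocation of appropriate resources", with the allocation qualified as being according to complexity. The matching objective is to explore whether PCI-derived complexity "could facilitate appropriate resource allocation; these resources being the time allocated to providing clinical care to the complex client or referrals completed".
- **Outcomes (section 2.9).** "The first secondary outcome is the addition of nursing care interventions after initial assessment", grouped as medication support, wound care, referrals and liaison, and others. "The second secondary outcome is the nursing care time added in minutes".
- **Analysis (section 2.10).** The first secondary outcome now covers subtraction as well: "modification of nursing interventions (addition or subtraction of nursing interventions"). For it, "between group comparisons will be performed on distribution of intervention categories". Clinical time, as a three-level variable, is compared between arms by ordinal regression. Age and nurse experience are covariates; gender, reason for referral, group and complexity rating are factors.
- **Complexity rating (section 2.9).** The primary outcome, low, moderate or high, is obtained with the PCI in the intervention arm and by nurse judgment alone in the control arm.

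**The concern.** The hypothesis has two parts that the outcomes do not carry. *Appropriate* is never given a criterion, and *according to complexity* is a statement about how care varies across clients, not about its average or mix in an arm. If the stated tests are run exactly as written, a significant group term could be reported as better allocation when care had simply risen for everyone. A null group term could be reported as no benefit when care had moved from less complex to more complex clients. Either way, the conclusion on resource allocation would rest on a test of something else.

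**Working it through.** **1. The plan's own figure.** The only sample size concerns the primary outcome: 23.1% (control) versus 5.7% (intervention) rated high. The odds ratio is (0.231/0.769)/(0.057/0.943) = 4.97, as stated. A two-sided Fisher exact test at 0.05 has power 0.795 with 68 per arm and 0.802 with 69, so 69 per group (138 in total) reproduces. The point below does not depend on that size; it uses the two percentages and the target of 90 per group.

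**2. Hypothesis against tests.**

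| Needed for the hypothesis | Stated |
|---|---|
| A definition of appropriate care, or a reference for care needed at each complexity level | None |
| Complexity measured the same way in both arms | PCI in one arm, nurse judgment in the other |
| A contrast of how care varies with complexity, by arm | Category mix by arm; group and complexity as separate factors for time, with no interaction stated |

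**3. What the group term can see.** Assumed inputs: three equally common complexity levels, and control-arm time split 1/3, 1/3, 1/3 over the three time levels (least to most).

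- *(a) Pure reallocation.* In the PCI arm, high-complexity clients move to 1/6, 1/3, 1/2, low-complexity clients move to 1/2, 1/3, 1/6, and moderate clients are unchanged. The arm-wide share at the top time level is (1/2 + 1/3 + 1/6)/3 = 1/3, and the other two levels are also 1/3. The arm totals equal control.
- *(b) Uniform extra time.* Every PCI-arm client moves to 1/6, 1/3, 1/2. The cumulative odds ratios against control are (5/6 ÷ 1/6)/(2/3 ÷ 1/3) = 2.5 and (1/2 ÷ 1/2)/(1/3 ÷ 2/3) = 2.

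Proportional-odds regression with group and complexity as factors, 90 per arm, 300 simulated trials per scenario:

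| Scenario | Group term significant | Group-by-complexity term significant (if added) |
|---|---|---|
| (a) Pure reallocation | about 4% | about 52% |
| (b) Uniform extra time | about 82% | about 5% |

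Simulation error is at most about 3 percentage points (√(0.52 × 0.48/300) = 0.029). The simulation is kind to the plan, because it gives both arms the same complexity scale.

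**4. What the actual complexity factor does.** Randomization should give both arms a similar share of clients whom nurse judgment would rate high, here 23.1%. If the PCI labels 5.7% high, then at least 0.231 − 0.057 = 0.174 of PCI-arm clients (0.174 × 90 ≈ 16 of 90) would be high by judgment but carry a lower label. They form at least 0.174/0.943 = 18.5% of the not-high group in the PCI arm and none of it in the control arm. Suppose the PCI changes nobody's time, and these clients receive D more minutes than clients judged not high. The not-high groups would then still differ by about 0.185 × D. The documents give no value for D. The point is that equal labels do not mean like clients, so adjusting for the label can create or hide a group difference. This takes the early percentages at face value and merges low and moderate.

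**The case against.** The strongest reply is that complexity is already in the time regression, so the planned comparison is not one of raw totals, and that model terms such as an interaction may be settled in an analysis plan that is not shown. The first half is true but does not help: as a separate factor, complexity leaves the group term as an average shift, and the rating is not on one scale across arms. The second half is fair as far as it goes. However, an interaction with this rating would inherit the same defect, and the category comparison has no stated complexity term.

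The objective is also exploratory, and section 2.6 describes a pilot. That limits the weight of the point, although section 1.5 still states a formal null and section 2.10 a 0.05 threshold.

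A reader might infer more than the documents support:

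- *That the outcomes only count how much care is added.* They do not. The first is compared by type, and section 2.10 includes subtraction.
- *That the plan treats more care as success, so the PCI is penalized for adding less.* No section sets a direction. Section 3 does expect less duplication of referrals, which sits awkwardly with an additions-only outcome, but that is not a success criterion.
- *That 5.7% versus 23.1% shows better targeting would mean less care.* The two percentages come from different yardsticks and say nothing about minutes.
- *That the abstract claims appropriate allocation.* It states an aim about resource allocation, without that qualifier.
- *That the nurse's own rating gives a ready-made test of matching.* Section 2.10 does use it as the criterion for PCI cut-offs, but it is the judgment the PCI is meant to support, and section 2.8 has the allocation envelope opened before the study forms are completed. If nurses follow the PCI where it differs from their first view, care would track that rating less closely even when the PCI works.

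**Conclusion.** The mismatch holds. The stated secondary outcomes and tests can show a change in the amount or type of care; they cannot show that care is better matched to complexity. The complexity factor does not close the gap.

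The size given is illustrative. With 90 per arm, the group term reacts to an exactly offsetting reallocation at roughly the false-positive rate (about 4%) and to uniform extra time in about 82% of trials. The effects were assumed, and scenario (a) was built to cancel. It shows what the test cannot see, not how likely that outcome is.

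The primary outcome comparison is untouched by this point. It deserves correction because the secondary conclusion, as worded, would go beyond its evidence whichever way the tests fall.

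**What to change.** 1. Restate the secondary hypothesis in section 1.5, and the conclusion drawn from it, as the effect of adding the PCI on the amount and type of care allocated. Do not describe an arm difference as more or less appropriate allocation.
2. Make sections 2.9 and 2.10 agree that the first secondary outcome covers both additions and subtractions.
3. Estimate the arm difference in clinical time without conditioning on the arm-specific complexity rating.
4. If matching remains of interest, report a group-by-complexity contrast as exploratory, with a confidence interval, on a measure obtained the same way in both arms and ideally recorded before the allocation envelope is opened. State that a nurse-judged scale is an imperfect yardstick whose gradient can flatten if nurses follow the PCI over their own judgment.

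Items 1 to 3 need only changes to wording and the model. Item 4 may need a change in the order of recording. Section 2.8 suggests that a nurse rating is taken in both arms, but this should be confirmed against the survey forms, which are not shown. Precision would be limited: power was about 52% under the assumptions above. The main cost is a more modest secondary conclusion.
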